### Data collection

Research data will be collected from 01 May 2021 to 30 October 2022. The Primary Investigator (PI) will use the Research Electronic Data Capture (REDCap) software as the primary data collection tool. At baseline, the PI will capture demographic, clinical, calculated TIMI and GRACE scores, laboratory test results, ECG, echocardiographic, coronary angiographic, revascularisation and discharge medication data shown in Appendix B. The PI will create and access a reference list of the study participants’ hospital numbers and specific study numbers. The PI will retrieve these from the relevant progress notes, National Health Laboratory Service (NHLS) lab track, electronic medical records, and coronary angiogram report database of the division of cardiology at CMJAH.

The PI will telephonically contact all participants or their designated family members to monitor general well-being, medication compliance, outpatient cardiac clinic visits and cardiac-related re-admissions. When re-admitted to CMJAH, the PI will access the relevant hospital records to ascertain whether our study’s outcomes of interest occurred. Participants will be deemed compliant with medication if they say so during the telephonic interviews. The telephonic interviews will follow a closed-ended structured questionnaire, as depicted in Appendix C. Each participant will receive a telephonic interview call at 30 days, three months, six months and twelve months after the index hospital discharge date. All participants will be given the PI’s phone number and business card and encouraged to save the number on their cellphones when they sign informed consent forms so that doctors from other hospitals can contact the PI for cardiac-related referrals to CMJAH.

The PI will obtain the peak values of serum hs-cTnI, serum CRP and SUA from routine blood tests drawn at baseline for all participants. Automated messages generated through REDCap will be sent to remind both the PI and the participants of their scheduled outpatient clinic visits a week before the visits.

An experienced research sonographer will perform standardised echocardiograms during the outpatient clinic visits three months and one year after the index discharge. The two cardiologists who supervise the study will verify all echocardiograms. Appendix D shows the left ventricular parameters and valve analysis that will be recorded.

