## Methods

### Study aims

This study aims to determine the clinical outcomes of an acute STEMI within one year of clinical presentation to the division of cardiology at the CMJAH. The study also evaluates the association between baseline serum cardiac biomarkers of myocardial infarction and all-cause mortality within a year of acute STEMI.

The primary objective is:

To determine the all-cause mortality rate of an acute STEMI at 30 days, three and six months, and one year after the index presentation.

The secondary objectives include:

To determine the rates of cardiac-related re-hospitalisation, heart failure, angina, major bleeding, thromboembolism, non-fatal arrhythmias (namely, atrial fibrillation, ventricular tachycardia, and complete heart block) and planned or unplanned repeated revascularisation at 30 days, three and six months and one year after the index STEMI at CMJAH.To assess the relationship between all-cause mortality and the peak serum hs-cTnT, CRP and SUA measured on admission.To describe the baseline clinical characteristics of STEMI patients in our setting.To compare the clinical outcomes between STEMI patients who received thrombolysis, PCI, a pharmaco-invasive strategy and those who underwent no reperfusion at 30 days, six and three months, and one year after the index STEMI.To determine the baseline clinical predictors of all-cause mortality at 30 days, three months, six months and one year after the initial STEMI.To describe the adjuvant medical care provided and medication compliance rates at 30 days, three months, six months and one year after the index discharge from the hospital.

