### Study design and setting

The study is a single-centre, observational, prospective cohort of all consecutive individuals with an acute STEMI diagnosis presenting to the CMJAH. The study will take place in the division of cardiology at the CMJAH, a academic state-owned tertiary PCI-capable healthcare facility in Johannesburg, South Africa. Participants will be followed over one year, and clinical outcomes will be measured at 30 days, three months, six months and one year from the index date of hospital discharge. The first day after hospitalisation will be considered day one of the follow-up.

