### Statistical analysis

Stata Corp. IC Version 16.1 will be used for all statistical analyses. Normally distributed continuous data will be presented as means with standard deviations (± SD). Continuously skewed data will be reported as medians with interquartile ranges (IQR). We will express categorical data as numbers and percentages. For intergroup comparisons, the student’s unpaired t-test and one-way analysis of variance (ANOVA) with Fisher’s test will be used for continuous variables and the chi-square test for categorical variables. Demographic and clinical profiles will be presented in frequency tables. Univariate and multivariate cox regression analyses will be used to determine the baseline clinical predictors of mortality. Survival curves generated by the Kaplan-Meier method will be used to determine the crude one-year survival among the different reperfusion groups and compared with log-rank tests. All variables will be expressed with their hazard ratio and 95% confidence intervals. For all tests, a p-value < 0.05 will be considered statistically significant.

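### Mortality and its predictors are timed from presentation in one section and from discharge in another, and the single baseline record mixes variables that suit only one of these clocks.

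*Protocol article*

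**What the plan says.** Two time origins appear in the Methods of the protocol article.

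- Presentation. Study aims words its main aim this way: "To determine the all-cause mortality rate of an acute STEMI at 30 days, three and six months, and one year after the index presentation". Among the secondary aims in that section, the one on predictors reads: "To determine the baseline clinical predictors of all-cause mortality at 30 days, three months, six months and one year after the initial STEMI".
- Discharge. Under Study design and setting, "clinical outcomes will be measured at 30 days, three months, six months and one year from the index date of hospital discharge", and then: "The first day after hospitalisation will be considered day one of the follow-up". Data collection also times the telephone interviews from the discharge date.

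Data collection describes the baseline record: "At baseline, the PI will capture demographic, clinical, calculated TIMI and GRACE scores, laboratory test results, ECG, echocardiographic, coronary angiographic, revascularisation and discharge medication data". Statistical analysis gives the model: "Univariate and multivariate cox regression analyses will be used to determine the baseline clinical predictors of mortality". It states no time origin for that model and does not separate variables known at presentation from those fixed later in the stay.

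**The concern.** A Cox model assumes that a fixed covariate is known at time zero. Demographics, history and the first ECG meet that condition on either clock. Discharge medication meets it only on the discharge clock. Angiographic and revascularisation findings also come after presentation, and a patient has to live long enough to have them.

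One undivided baseline set therefore cannot serve both clocks. On the presentation clock, an in-hospital death must either be coded as not having the discharge drug or be left missing. The first choice makes survival to discharge look like a drug effect (immortal-time bias). The second removes the early deaths from the model. On the discharge clock neither problem arises, but deaths before day one are not counted, although the primary and predictor objectives ask for mortality from presentation. Both the mortality estimate and the reading of the predictors depend on a choice that the article makes in two incompatible ways.

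**Working it through.** **Plan's own figure.** The article gives no figure on this point to reproduce. The planned 355 participants are used below only as the cohort size.

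**Inputs**
- n = 355 (Study sample size calculation).
- One-year mortality after discharge: 6.7%, the outpatient rate that the Background gives from the earlier South African registry. Using it for this cohort is an assumption.
- In-hospital mortality among enrolled patients, m: not given. Assumed 1% to 5%.
- Share of discharge survivors prescribed the drug, c: not given. Assumed 60% to 90%.
- True hazard ratio of the drug: 1.

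**Step 1. What the choice of clock does to one-year mortality.** Ignoring the few days' difference in the end date, mortality from presentation is m + (1 − m) × 0.067.
- m = 1%: 0.01 + 0.99 × 0.067 = 7.6%. In-hospital deaths are 0.01 / 0.0763 = 13% of all deaths.
- m = 5%: 0.05 + 0.95 × 0.067 = 11.4%. In-hospital deaths are 0.05 / 0.1137 = 44% of all deaths.

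The discharge clock gives 6.7% in both cases.

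**Step 2. Presentation clock, in-hospital deaths coded as no drug (closed form).** Risk with the drug is 6.7%. Risk without it is [m + (1 − m)(1 − c) × 0.067] / [m + (1 − m)(1 − c)].
- m = 1%, c = 60%: (0.01 + 0.396 × 0.067) / 0.406 = 0.0365 / 0.406 = 9.0%. Risk ratio 6.7 / 9.0 = 0.74.
- m = 5%, c = 90%: (0.05 + 0.095 × 0.067) / 0.145 = 0.0564 / 0.145 = 38.9%. Risk ratio 6.7 / 38.9 = 0.17.

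**Step 3. The same setting by simulated Cox model.** About 300 runs per cell, with in-hospital deaths spread over days 0.5 to 7. Entries are the median apparent hazard ratio and the share of runs falsely protective at p < 0.05.

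| In-hospital mortality (assumed) | 60% prescribed | 80% prescribed | 90% prescribed |
|---|---|---|---|
| 1% | 0.74 (13%) | 0.56 (30%) | 0.41 (49%) |
| 3% | 0.49 (55%) | 0.30 (90%) | 0.19 (98%) |
| 5% | 0.33 (90%) | 0.22 (>99%) | 0.14 (100%) |

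Some runs in the 90% column were lost to non-convergence or to no events in one group (224 of 300 remained at 5%). A separate simulation over the same range gave 0.13 to 0.75.

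**Step 4. Presentation clock, in-hospital deaths left missing and dropped.** The apparent hazard ratio is 0.97 to 1.07. There is no false protection, but the model now covers discharge survivors only.

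**Step 5. Discharge clock, patients discharged alive.** The apparent hazard ratio is 1.00 to 1.01, falsely protective in 3% to 6% of runs. The bias is absent.

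**The case against.** The strongest reply is that the article never puts discharge drugs into the Cox model. Data collection lists what is captured, not what is modelled. Medication has its own descriptive objective, timed from discharge: "To describe the adjuvant medical care provided and medication compliance rates at 30 days, three months, six months and one year after the index discharge". The predictors that the Background expects are age, sex, diabetes and heart failure on admission. A covariate list and landmark rules may properly sit in a fuller document that is not shown. All of this stands. A reader might infer that null drugs will look strongly protective in this study; the documents do not support that.

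A second reply is that the discharge clock in Study design and setting removes the bias. That is right, as step 5 shows, but it does not settle the matter. Study aims states the other clock, and on the discharge clock in-hospital deaths precede day one.

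Third, the written-consent requirement may exclude some patients who die early. That would shrink the bias; it would not remove it unless no enrolled patient died in hospital.

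Fourth, a remedy that barred every in-hospital variable from presentation-clock models would clash with stated objectives. Study aims asks for peak troponin, CRP and uric acid and for a comparison of reperfusion groups. This also stands, and the fix allows for it.

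**Conclusion.** The point holds as a stated conflict with a conditional consequence. The two time origins contradict each other, and the baseline record contains variables that are valid at time zero on only one of them.

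If the presentation clock is used, discharge drugs are entered and in-hospital deaths are coded as no drug, a null drug can show a hazard ratio of about 0.13 to 0.75. That range rests on assumed in-hospital mortality of 1% to 5% and prescribing of 60% to 90%, neither of which the article gives. If those deaths are left missing, the hazard ratio stays near 1 but the population changes without notice. If the discharge clock is used, the bias is absent and the presentation-timed objective is not met; on the same assumptions, 13% to 44% of one-year deaths would go uncounted.

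Two stronger readings go too far. One is that the bias is certain. The other is that either handling of in-hospital deaths produces false protection: only the no-drug coding does. The hazard ratios above were worked out for discharge drugs alone. Angiography and revascularisation raise the same timing question, but no size is claimed for them.

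**What to change.** Reconcile Study aims with Study design and setting, and state time zero for each analysis under Statistical analysis:

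1. Mortality and predictor models on the presentation clock: count in-hospital deaths and use only variables known at presentation.
2. Discharge medication, and other variables fixed during the stay: analyse from discharge, in patients discharged alive.
3. Peak biomarkers and reperfusion groups, which the objectives require: keep them, using a stated landmark or time-dependent variables.

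This needs a short revision of the analysis text and no new assessments, provided that the dates of presentation, procedures, discharge and death are recorded. The landmark or time-dependent handling adds some analysis work. The downside is that discharge variables can then be interpreted only for patients who survive to discharge.

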This study has several potential limitations. First, it is a single-centre study and thus prone to selection bias. Second, its observational nature may not allow us to control for unmeasured confounders that may contribute to the clinical outcomes observed. Third, although participants’ and participants’ next of kin’s cellphone numbers will be recorded, the prospective nature of the study makes it susceptible to loss to follow-up. Fourth, the follow-ups will be conducted through structured telephonic interviews, which may lead to patients omitting vital health data and, thus, under-reporting adverse cardiovascular events of interest to this study. Finally, the study site’s emergency department was not fully functional due to a fire incident that occurred prior to the start of the study, which may limit the number of participants presenting at our facility.

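### A death outside the study hospital is actively learned of only through an answered telephone call, so one-year mortality is likely to be understated if those who die are lost more often

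*Protocol article*

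**What the plan says.** The primary objective in the Protocol article (Study aims) reads: "To determine the all-cause mortality rate of an acute STEMI at 30 days, three and six months, and one year after the index presentation".

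Four ways in which information can reach the investigator after discharge are described under Data collection:

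- **Telephone.** "Each participant will receive a telephonic interview call at 30 days, three months, six months and twelve months after the index hospital discharge date". The call may go to a relative: "The PI will telephonically contact all participants or their designated family members to monitor general well-being".
- **Study-hospital records.** "When re-admitted to CMJAH, the PI will access the relevant hospital records".
- **Clinic visits.** "An experienced research sonographer will perform standardised echocardiograms during the outpatient clinic visits three months and one year after the index discharge". Automated reminders go out a week before.
- **Outside doctors.** Participants are asked to save the investigator's number "so that doctors from other hospitals can contact the PI for cardiac-related referrals to CMJAH".

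The same section names the hospital's electronic medical records and the NHLS lab track as sources of baseline data. The limitations paragraph of the Discussion says that numbers for participants and next of kin are recorded, yet "the prospective nature of the study makes it susceptible to loss to follow-up". It also expects adverse cardiovascular events to be under-reported by telephone. It does not discuss missed deaths.

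Statistical analysis names Kaplan-Meier curves for the reperfusion groups and Cox regression for predictors. The article states no censoring rule for participants who cannot be reached.

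**The concern.** The four routes differ in what they can reveal. A clinic visit shows that an attender is alive, but a missed visit does not show that someone has died. The record check depends on a re-admission to this hospital, so a death at home or in another hospital does not trigger it. The outside-doctor route is passive and limited to cardiac referrals, whereas the endpoint is death from any cause. For a death outside the study hospital, the one active route left is a call that a relative must answer.

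A participant who has died cannot answer, so losing contact may well be related to the endpoint. If it is, the primary estimate is pulled downward whether the lost participants are censored, dropped or counted as alive. A confidence interval reflects sampling error only and would not show this. The Background hypothesises mortality similar to that in high-income countries. If local mortality is in fact higher, missed deaths would move the result towards that hypothesis.

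**Working it through.** **Inputs from the Protocol article.** Sample size 355 (Study sample size calculation). Reference one-year mortality 6.7%, from the South African registry quoted in the Background.

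**Assumptions, not in the documents.** Share lost L = 10% or 20%. Ratio R of one-year death risk in the lost to that in those reached = 2 or 3. Loss occurs early, so none of the deaths among the lost are counted.

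The plan gives no figure for loss or missed deaths, so there is no stated number to reproduce.

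**1. If 6.7% is the mortality among those reached**, true mortality = (1 − L) × 6.7% + L × R × 6.7%.

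| L | R | Calculation | True | Understated by |
|---|---|---|---|---|
| 10% | 2 | 0.9 × 6.7 + 0.1 × 13.4 | 7.4% | 0.7 points |
| 10% | 3 | 0.9 × 6.7 + 0.1 × 20.1 | 8.0% | 1.3 points |
| 20% | 2 | 0.8 × 6.7 + 0.2 × 13.4 | 8.0% | 1.3 points |
| 20% | 3 | 0.8 × 6.7 + 0.2 × 20.1 | 9.4% | 2.7 points |

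With R = 1 the formula returns 6.7%: no bias.

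**2. If 6.7% is the true mortality instead**, observed = 6.7% / (1 − L + L × R).

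- L = 10%, R = 2: 6.7 / 1.1 = 6.1%
- L = 10%, R = 3: 6.7 / 1.2 = 5.6%
- L = 20%, R = 2: 6.7 / 1.2 = 5.6%
- L = 20%, R = 3: 6.7 / 1.4 = 4.8%

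**3. In numbers of deaths.** 355 × 0.067 = 23.8, about 24 deaths. If 20% of them (about 5) are never learned of and those participants are censored at the start, observed = 0.067 × 0.8 / (1 − 0.067 × 0.2) = 5.4%, about 1.3 points low.

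**4. Against sampling error.** The 95% half-width at 6.7% and n = 355 is 1.96 × √(0.067 × 0.933 / 355) = 2.6 points. Most of the scenarios lie inside it; the most extreme one in step 1 just reaches it.

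**5. What bounds would look like without further tracing.** With 10% unresolved and 6.7% among the rest, all alive gives 0.9 × 6.7 = 6.0%, and all dead gives 6.0 + 10 = 16.0%. Bounds this wide say little, so the unresolved group should be made as small as possible first.

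**The case against.** A reader might infer that vital status is sought only by telephone, that unreachable participants are censored as alive, and that mortality is therefore understated. The documents do not support that reading.

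- Telephone is not the only contact. Clinic visits with reminders and a record check on re-admission are also planned.
- No censoring rule is stated. Kaplan-Meier is named for the reperfusion groups, not for the overall primary rate. The follow-up questionnaire (Appendix C) is not shown, and an article may leave tracing and censoring rules to the full protocol or analysis plan.
- Bias requires loss that is related to death. Recording next-of-kin numbers is a real safeguard: the participant's phone and the relative's must both fail, and fail more often after a death.

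It is also tempting to set the possible bias against the 3.7-point difference between the 6.7% and 10.4% quoted in the Background. The 10.4% is given there as an overall death rate from a single referral centre. The article does not call it a registry figure or state a one-year horizon for it, and it plans no test against either number. The difference is no decision threshold.

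The authors disclose loss to follow-up and the limits of telephone interviews, and the passages do not contradict each other. All of this stands, and it makes the point conditional. It does not remove the point: the article sets out its follow-up routes in detail, none of them actively finds a death elsewhere when the calls go unanswered, and disclosing a limitation does not reduce it.

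**Conclusion.** The point holds in conditional form. As described, ascertainment of the primary endpoint outside the study hospital rests on answered calls, and mortality is likely to be understated if loss of contact is commoner among those who die. The size cannot be fixed from the documents. Under the assumed loss rates and risk ratios it is 0.7 to 2.7 points at 6.7% mortality among those reached, and zero if loss is unrelated to death. Only the upper end is comparable with the sampling error, but a larger sample would not remove it. This is a weakness in ascertainment that can be reduced cheaply; it is neither a contradiction in the plan nor evidence that the result will be wrong.

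**What to change.** At study end, for every participant whose vital status is not confirmed at 12 months:

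1. Search the hospital electronic records and the NHLS lab track, whether or not a re-admission was reported. Any later entry shows the participant alive on that date, or records the death.
2. Use the resulting date of death, or date last known alive, in the primary estimate.
3. Report one-year mortality with two bounds, taking those still unresolved as all alive and as all dead, and state how many they are.

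Optionally, add an enquiry to civil death registration where consent and access allow. The documents do not mention such a source, so its availability is an assumption, and consent may no longer be obtainable from participants already enrolled who have died or cannot be reached.

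**Cost.** Some investigator time; the first three steps use systems the study already uses. The records may miss deaths outside the network. A search may also find deaths more readily than survivors, which could tilt the estimate the other way. The bounds cover both directions.

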### Study sample size calculation

A minimum sample size of 355 participants in one year is required to achieve a study power of at least 80% for statistical significance. Using Cochrane’s formula, a minimum sample size of 182 participants is required for statistical significance with a 95% confidence interval and a 5% margin of error to assess the clinical outcomes at 30 days. Appendix E illustrates the formulae and sample size calculations used.

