Data from the South African Registry of Acute Coronary Events multinational Survey of current management Strategies (ACCESS) reported that the thirty-day and one-year outpatient all-cause mortality rates in STEMI patients were 2.4% and 6.7%, respectively [6]. The French Registry on Acute ST-elevation Myocardial Infarction (FAST-MI) of 2008 reported that in patients treated with thrombolysis, the thirty-day mortality rate is 9.2% without PCI and 3.9% when rescue PCI is subsequently performed (p = 0.044) compared to 2.8% in those who undergo a pharmaco-invasive approach (p = 0.147) [7]. According to the FAST-MI of 2008, the crude one-year survival rate is 78.5% in patients without reperfusion, 93.6% for thrombolysis, and 91.8% for PPCI (p < 0.001 for overall comparison; p = 0.31 for thrombolysis vs PPCI). When compared to other regions in SSA, the crude one-year mortality rate of 6.7% reported in the South African ACCESS registry was lower than the overall death rate of 10.4% reported in a single national referral centre study conducted in the Intensive Care Unit of Abidjan Heart Institute, in Côte d’ Ivoire [8].

An age of ≥ 70 years, female gender and heart failure on admission are significant factors predictive of mortality at thirty days and one-year follow-up of STEMI, irrespective of myocardial revascularisation strategy [8]. Diabetes mellitus on admission and a history of stroke or transient ischaemic attack (TIA) are also associated with a higher risk of death at one year [6]. In SSA, delayed access to emergency medical services (EMS) and healthcare facilities with reperfusion therapy limits favourable outcomes in STEMI patients [9]. In a local prospective cohort study at a single tertiary centre involving 100 STEMI patients, Meel et al. reported that only 37% of eligible patients received fibrinolytic therapy [10]. Only 3% received the medication within one hour. The median total time delay to administering a fibrinolytic agent was 270 min (45–584), with patient and transport delays being the most crucial reasons. For fibrinolytic therapy not given within one hour of hospital arrival, the calculated number of lives lost due to these delays was 32 patients per 1000 treated.

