This study seeks to determine the event rates of crude mortality, crude survival, re-hospitalisation, heart failure, angina, major bleeding, thromboembolism, arrhythmias and revascularisation at 30 days, three months, six months and one year after the index STEMI. We seek to compare these clinical outcomes between four primary STEMI sub-groups (i.e., those who receive fibrinolysis vs. no fibrinolysis vs. PCI vs. no PCI) in our local practice and compared with those reported in HIC and other regions of SSA. We also aim to evaluate the association between the peak baseline measurements of serum hs-cTnT, serum CRP, SUA and clinical outcomes within a year.

We hypothesise that the thirty-day and one-year crude mortality rates for STEMI patients observed in our setting would follow similar trends to those in HIC with no significant differences. We anticipate that the various STEMI management therapies provided in our practice would offer similar one-year all-cause mortality and morbidity benefits, irrespective of the revascularisation strategy used when comparing fibrinolysis vs. PPCI vs. fibrinolysis followed by PCI among groups. In our setting, we expect that advanced age, female gender, diabetes mellitus and heart failure on admission play critical roles in predicting death at 30 days and one year.

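### The similarity hypotheses are paired only with difference tests and no margin, and the unspecified 80% power cannot apply to fibrinolysis versus primary PCI at the rates the article cites

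*Protocol article*

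**What the plan says.** The primary objective (Methods, Study aims) is to determine all-cause mortality at 30 days, three months, six months and one year. Comparing outcomes between reperfusion strategies is a secondary objective.

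The hypotheses stand at the end of the Background. The first expects that 30-day and "one-year crude mortality rates for STEMI patients observed in our setting would follow similar trends to those in HIC with no significant differences". The second expects that the therapies "would offer similar one-year all-cause mortality and morbidity benefits, irrespective of the revascularisation strategy used", and names fibrinolysis, primary PCI and fibrinolysis followed by PCI. Neither carries a margin.

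The Statistical analysis section lists t-tests, ANOVA, chi-square tests, Cox regression, and Kaplan-Meier curves compared by log-rank tests. Hazard ratios with 95% confidence intervals are planned. The decision rule is: "For all tests, a p-value < 0.05 will be considered statistically significant".

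The Study sample size calculation section states "A minimum sample size of 355 participants in one year is required to achieve a study power of at least 80% for statistical significance". It adds that, for clinical outcomes at 30 days, "a minimum sample size of 182 participants is required for statistical significance with a 95% confidence interval and a 5% margin of error". It then refers onward: "Appendix E illustrates the formulae and sample size calculations used". That appendix is not shown.

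**The concern.** A difference test can give evidence of a difference. Its failure to reject says little about similarity unless the study was large enough to exclude differences that matter. Here the first hypothesis is itself worded as non-significance, so p > 0.05 is the result that fits it, and a small study produces that result easily.

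The power sentence adds to the risk. It names no comparison, so a reader may attach the 80% to the hypotheses in the Background, which are the only ones the article states. The Abstract says that the comparison of reperfusion strategies may guide clinicians where access to PCI is limited. A non-significant fibrinolysis versus PCI result, from a study described as having at least 80% power, could then be taken as showing that the strategies are interchangeable, when the data would still be compatible with large differences either way.

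**Working it through.** **The plan's own figures.** The 355 cannot be reproduced from the article, because no effect, comparator or group split is given. The 182 follows from Cochran's formula, n = 1.96² p(1−p)/0.05², only if p is about 13.7%: 3.8416 × 0.137 × 0.863 / 0.0025 = 181.7. The article does not state the proportion used.

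**Inputs for the check**
- One-year mortality, from the French registry survival figures in the Background: thrombolysis 100 − 93.6 = 6.4%; primary PCI 100 − 91.8 = 8.2%.
- Significance level 0.05 (Statistical analysis). Sidedness is not stated; two-sided is assumed.
- Group sizes are not given. Equal splits of 355 into two, three or four groups are assumed: 177, 118 or 89 each.

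**Power for 6.4% versus 8.2%.** The difference is 0.018 and the mean rate is 0.073. With n per group, SE₀ = √(2 × 0.073 × 0.927 / n) and SE₁ = √((0.064 × 0.936 + 0.082 × 0.918) / n). Power is Φ((0.018 − 1.96 SE₀)/SE₁), plus the small opposite tail Φ((−0.018 − 1.96 SE₀)/SE₁).

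| n per group | SE₀ | SE₁ | Main tail | Both tails | 95% CI half-width (1.96 SE₁) |
|---|---|---|---|---|---|
| 177 | 0.02765 | 0.02764 | 9.5% | 10.0% | 5.4 points |
| 118 | 0.03387 | 0.03385 | 7.6% | 8.3% | 6.6 points |
| 89 | 0.03900 | 0.03897 | 6.7% | 7.5% | 7.6 points |

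A true difference of this size would therefore give p > 0.05 at least 90% of the time.

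**Sample size for 80% power.** n = [(1.96 √(2 × 0.073 × 0.927) + 0.8416 √(0.064 × 0.936 + 0.082 × 0.918)) / 0.018]² = [(0.7210 + 0.3094)/0.018]² ≈ 3,278 per group.

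**What showing similarity would need.** The article gives no margin, so the following are illustrations. Take equal true rates p, one-sided 0.025, 80% power and margin m: n = 2p(1−p)(1.96 + 0.8416)²/m².
- m = 5 points, p = 6.7%: 393 per group.
- m = 5 points, p = 8.2%: 473 per group.
- m = 3 points, p = 6.7%: 1,091 per group.

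Each is more per group than the 355 planned in total. Put another way, if both groups of 177 had an observed mortality of exactly 6.7%, the interval on the difference would be ±1.96 √(2 × 0.067 × 0.933/177) = ±5.2 points, which does not fit inside a 5-point margin.

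**What 355 does give for the primary objective.** The Background reports that South African "thirty-day and one-year outpatient all-cause mortality rates in STEMI patients were 2.4% and 6.7%, respectively". Near those rates:
- 24 deaths of 355 (6.8%) by one year: exact 95% CI 4.4% to 9.9%.
- 9 deaths of 355 (2.5%) by 30 days: exact 95% CI 1.2% to 4.8%.

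**The case against.** The strongest reply is that the article never ties its 80% to these comparisons. It refers to Appendix E, which may name a contrast for which the figure is right, and an article may leave that to an appendix. This stands. A reader might infer that the 80% is false in general, and the text does not support that. Other cited contrasts do much better under the same equal-group assumption: no reperfusion (21.5%) versus primary PCI (8.2%) has 71% to 94%, no reperfusion versus thrombolysis (6.4%) has 83% to 99%, and 9.2% versus 2.8% at 30 days has 43% to 72%. A one-sample test of 10.4% against a fixed 6.7% has 75% at n = 355. Null results are therefore likely for differences of the fibrinolysis versus primary PCI size, but not for every comparison.

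Two further inferences about the 182 also fail. A reader might call it an arithmetic error, because none of the cited 30-day mortality rates yields it. But it is stated for 30-day clinical outcomes generally, which include re-hospitalisation, heart failure and angina, and a proportion near 13.7% could be one of those. A proportion of 50% with a finite population of about 345 also gives 182. A reader might also say that a 5-point margin is uninformative beside a 30-day mortality of 2.4%. That rate is a background registry figure, not a declared assumption, and the half-width actually obtained at 2.4% is 2.2 points with 182 participants and 1.6 with 355. The planning margin has no bearing on whether group comparisons come out null.

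Finally, the article says it hypothesises and anticipates; it sets no rule that p > 0.05 proves similarity, describes no formal test against high-income countries, and already plans hazard ratios with confidence intervals. All of that is fair. It does not remove the mismatch: the hypotheses assert similarity, the only stated criterion is a significance threshold for differences, and no margin says how close is close enough.

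**Conclusion.** The concern holds in this limited form. The similarity hypotheses cannot be supported by the tests planned, because those tests look for differences and no margin is set. The 80% power is unspecified in the article, not shown to be wrong, but it cannot describe fibrinolysis versus primary PCI at the cited one-year rates: power there is about 7% to 10%, and roughly 3,278 per group would be needed for 80%. The interval on the mortality difference, ±5.4 to ±7.6 points, is about as wide on each side as the mortality rates being compared.

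These figures assume two-sided testing, equal groups and true rates equal to the French registry's. Unequal groups within the same total would lower the power further. The conclusion about the missing margin needs no numerical assumption and does not depend on Appendix E. The primary objective, estimating overall mortality, is not undermined: 355 participants give useful precision for it.

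**What to change.** 1. **Hypotheses (Background).** Recast both as estimation: one-year mortality will be estimated overall and by strategy, and set beside published rates, with confidence intervals. Remove non-significance as the expected finding.
2. **Statistical analysis.** Report each between-strategy mortality difference with its 95% confidence interval, alongside the hazard ratios already planned. State that similarity will be claimed only if that interval lies inside a prespecified, justified margin, and acknowledge that 355 participants are unlikely to meet a narrow one.
3. **Study sample size calculation.** State the precision for the primary objective, for example an exact 95% CI of 4.4% to 9.9% if 24 of 355 die by one year and 1.2% to 4.8% if 9 of 355 die by 30 days. Name the endpoint, contrast and effect to which the 80% applies, or delete the figure.

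This costs wording only: no extra participants, visits or data. The price is that the stated power will look less favourable and that similarity between strategies may not be claimable.
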